**Headteachers**

Information about the school environment in relation to opportunities for physical activity and current health-related policies within each school will be self-reported by headteachers in questionnaires.

**Parents**

Information about family background, lifestyle, the child’s physical activity, health, and possible medical diagnoses or disabilities, including neurodevelopmental disorders, will be self-reported by parents in questionnaires.

### Process evaluation

The process evaluation includes exploring the implementation of the intervention, with a focus on fidelity, dose, feasibility, acceptability, and contextual factors [45]. A combination of qualitative and quantitative methods will be used.

#### Fidelity and dose

Fidelity will be assessed through structured documentation by the teachers involved in delivering the intervention. Teachers will be asked to document all performed activities. For the physical activity sessions, the teachers will document the type and intensity of the activities. In addition, the teachers will document any adaptations made to the intervention protocol and the reasons for these adaptations. Implementation dose will be assessed as the dose delivered (the number of sessions) and the dose received (student participation), provided by teachers.

#### Feasibility, acceptability and context

The feasibility, acceptability and context will be explored through qualitative focus groups [46, 47] and/or interviews [48] with both students and teachers and through observations [49]. Students will be invited to focus groups (*n* = 20–30), with 6–8 participants in each focus group. A selection of students from each school will be invited to include a balanced gender representation, with a variation of engagement in the intervention activities. Teachers, headteachers and/or vice headteacher will be invited to interviews (*n* = 40) and/or focus groups. The selection will be based on male and female teachers, representing a variation of engagement in the delivery of the intervention and to represent various subjects. Interview guides focusing on the participants’ and teachers´ experiences of the intervention, including its different components, contextual factors, perceived facilitators and barriers, gender aspects, student needs, and potential influence of other aspects on intervention delivery and outcome, will be used.

In addition to interviews and focus groups, researchers will conduct observations during the intervention activities at all participating schools [49]. Researchers will conduct observations during a selection of intervention activities in all participating schools to deepen the understanding of how the intervention is implemented in practice. These observations will be systematically documented, focusing on adherence to the planned content, level of student engagement, teacher-student interaction, and any contextual influences that may have affected delivery. Field notes will be taken during or immediately after each observation, using a structured template to ensure consistency across settings.

### Sample size calculation

To obtain an effect size of intervention Cohen’s d = 0.35 in anxiety (based on a meta-analysis [18]) in a population with the average correlation between cluster of 0.02, a variance of 5 points in the primary outcome SCAS-S, a two-tailed significance test (α = 0.05), and a power of 80%, it is required to include at least 27 schools in the intervention group and 27 schools in the control group with 50 students from each school. Anxiety will be assessed with the questionnaire Spence Children’s Anxiety Scale Short Version (SCAS-S) [34].

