### Recruitment of schools, participants and setting

Schools from the Stockholm area within a 2–3 h drive from the Swedish School of Sport and Health Sciences and schools in the counties of Småland, located in the south of Sweden, will be invited by e-mail to the headteachers and vice headteachers. Schools with a sports profile and schools with a student population not speaking Swedish will be excluded.

Fifty-four schools with 2700 adolescents in grade eight, aged 14–15 years, will be included by the research group. Three waves are planned: the first in the school year of 2021–2022, the second in 2023–2024, and the third in 2024–2025. A one-year follow-up will be performed in the spring of 2025 and 2026.

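### The stated sample-size inputs do not give 27 schools per arm: Cohen's d = 0.35 needs about 7, and 27 is recovered only if 0.35 is a raw SCAS-S difference

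*Protocol article*

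**What the plan says.** The Sample size calculation section of the protocol article sets out a full list of inputs. The target effect is a Cohen's d of 0.35 for anxiety, credited to a meta-analysis. Clustering and spread are given as "average correlation between cluster of 0.02, a variance of 5 points in the primary outcome SCAS-S". The test is "a two-tailed significance test (α = 0.05"), with 80% power. The section then concludes: "it is required to include at least 27 schools in the intervention group and 27 schools in the control group with 50 students". The figure of 50 is per school. Recruitment of schools, participants and setting carries the same total forward: "Fifty-four schools with 2700 adolescents in grade eight, aged 14–15 years, will be included by the research group". The sample size section mentions no allowance for dropout, unequal school sizes, subgroup or interaction tests, or multiplicity.

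**The concern.** Two features of the paragraph do not fit together. First, a Cohen's d is already in standard deviation units, so no variance is needed to size the trial, yet one is supplied. Second, an effect of 0.35 SD with a correlation of 0.02 is not demanding for schools of 50 students, and 54 schools looks far too many for it.

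This calculation is the only justification given for the size of the trial. If the inputs and the result disagree, a reader cannot tell whether the trial was built to detect 0.35 SD or an effect less than half as large. That matters when either a null result or a small significant one is interpreted.

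**Working it through.** **Inputs** (Sample size calculation; the 1:1 allocation is in Study design): effect 0.35; correlation 0.02, read as the intracluster correlation (ICC); variance 5; two-sided alpha 0.05; power 80%; m = 50 students per school; k = 27 schools per arm. Equal school sizes and no gain from baseline adjustment are assumed.

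**Formulas**
- Students per arm without clustering: n = 2(1.96 + 0.8416)² / d² = 2 × 7.849 / d²
- Design effect: DE = 1 + (m − 1) × ICC = 1 + 49 × 0.02 = 1.98
- Schools per arm: k = n × DE / 50
- Check for few clusters: standard error of the standardised difference = √(2 × DE / (50k)), and power from a noncentral t on 2k − 2 degrees of freedom

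**Reading A: 0.35 is Cohen's d, as written**
- n = 15.698 / 0.1225 = 128.1; × 1.98 = 253.7; / 50 = 5.07, so 6 schools per arm by the normal approximation.
- With the t correction: k = 6, noncentrality 0.35 / 0.1149 = 3.05, power 78.4%; k = 7, noncentrality 0.35 / 0.1064 = 3.29, power 85.5%. Hence 7 per arm, or 14 schools and 700 students in all.
- At k = 27: noncentrality 0.35 / 0.05416 = 6.46, power above 99.9%.

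27 is not reproduced.

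**Reading B: 0.35 is a raw difference in SCAS-S points with variance 5**
- SD = √5 = 2.236; d = 0.35 / 2.236 = 0.157.
- n = 15.698 × 5 / 0.1225 = 640.7; × 1.98 = 1268.6; / 50 = 25.4 by the normal approximation.
- With the t correction: k = 26 gives 79.4%, k = 27 gives 81.0%.

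27 is reproduced as the smallest number reaching 80%.

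**Could an unstated allowance explain 27 under reading A?** Schools per arm at d = 0.35:

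| Change to the inputs | Schools per arm |
|---|---|
| 90% power | 8 |
| 99% power | 13 |
| 25 students analysed per school | 9 |
| 10 students analysed per school | 17 |
| Coefficient of variation of school size 1.0 (normal approximation) | about 8 |
| Fourfold inflation for an interaction (normal approximation) | about 20 |

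None of these reaches 27. The ICC would have to be about 0.19, more than nine times the stated 0.02.

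**What 27 × 50 per arm detects.** Solving the noncentral t for 80% power with ICC 0.02 gives a standardised difference of 0.155, which is 0.155 × 2.236 = 0.35 points if the SD is √5.

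**The case against.** The strongest defence is that the design may be right and only a label wrong. Under reading B the ICC, variance, power and school count all agree. A reader might infer from reading A that the stated 80% power is itself wrong. The document does not support that much, because it does not show whether 0.35 was entered as a standardised effect or as points. What it does show is that the listed inputs and the result are inconsistent. This defence stands and limits the claim.

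A second defence is that an article condenses a fuller protocol. It does not help here: the paragraph lists its inputs and says that they require 27 schools, and no ordinary allowance closes the gap.

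A reader might also infer that the trial is simply sized for 0.155 SD. That figure ignores the baseline value that the Data analysis section puts in every outcome model. If baseline explained 36% to 50% of the variance at both levels (an assumption), the detectable difference would fall to between 0.155 × √0.64 = 0.124 and 0.155 × √0.50 = 0.109. So 0.155 must be labelled as unadjusted.

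Finally, a reader might suspect that 5 is really an SD and that the trial is underpowered. With 0.35 points and an SD of 5, d = 0.07; 27 schools per arm would give about 24% power and 128 would be needed. No SD of 5 is stated anywhere, and this reading does not reproduce 27. It is a reason to confirm the input, not evidence of low power.

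**Conclusion.** The paragraph is wrong as written: its inputs and its school count cannot all be right. Either 0.35 is a Cohen's d, and the stated requirement is about four times what the inputs give (27 against 7 per arm); or 0.35 is in SCAS-S points, and the label Cohen's d and its link to the meta-analysis are wrong, with a planned effect of 0.157 SD, less than half of 0.35. The exact match makes the second a plausible source, but the document cannot settle it.

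The trial is not short of students for d = 0.35. Randomisation, the primary outcome and the analysis model are unaffected. The conclusion rests on reading the stated correlation as the ICC, on equal school sizes, and on no credit for baseline adjustment. Such credit would lower the requirement and widen the gap under reading A.

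**What to change.** Rewrite the sample size paragraph and leave enrolment as it is:

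1. State whether 0.35 is in SD units or SCAS-S points. If it is in points, remove the Cohen's d label and correct the attribution to the meta-analysis.
2. Confirm that 5 is the variance and not the SD, and name the SCAS-S scoring that it refers to.
3. Restate what the design delivers, for example: *27 schools per arm with 50 students each and an ICC of 0.02 give 80% power for a standardised difference of about 0.155 (unadjusted for baseline) and more than 99.9% power for d = 0.35.*

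The cost is one paragraph. No school or student needs to be added or removed.

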### Data management

The participants will be assigned a unique ID number and data will be de-personalised. The code linking the ID number to personal information will be stored separately on a secure server in a password-protected document. Original paper records will be securely stored at the Swedish School of Sport and Health Sciences to allow for quality control of electronic data entry. Data from the accelerometers will be transferred to electronic files, securely stored, and then deleted from the devices. All project data will be securely stored in password-protected electronic files on a server at the Swedish School of Sport and Health Sciences to prevent unauthorised access. Raw data files will be kept separate from those used in active analysis, and no files used in statistical analyses will contain any personally identifiable information. To reduce the risk of data loss, systematic backups will be performed throughout the data collection process, and data will be stored on servers that are backed up daily. Access to the data will be restricted to researchers directly involved in data entry or analysis. No data monitoring committee (DMC) will be established due to the trial’s low risk. Adverse effects will be monitored by the research group. No specific provisions for ancillary or post-trial care are planned. However, participants who suffer harm from trial participation will be covered according to the institution’s standard insurance.

### Data analysis

Baseline differences in continuous demographic variables between the intervention and control groups will be presented using means and standard deviations (SD) for normally distributed data and compared using independent t-tests. For non-normally distributed data, medians and ranges will be reported, with analyses conducted using non-parametric tests. Categorical variables will be described as proportions, and group differences will be examined using chi-square tests. The effects of the intervention on primary and secondary outcomes will be analysed through mixed-effects regression models with two hierarchical levels (individual and school), using post-intervention data and following the intention-to-treat approach. Initially, a crude model will be tested for each outcome at post-intervention, including group allocation as a predictor and adjusting for baseline values of the corresponding outcome. In a second model, gender and parental education will be added to the model. Interactions between group and gender, or group and parental education, will be tested and, if significant, analysed using stratified models All participants with baseline measurements will be included, and missing data will be addressed using multiple imputation The potential impact of missing data on the results will be evaluated through sensitivity analyses. Additionally, the analysis will be performed per protocol, including only those participants with high fidelity to the intervention components. All analyses will be performed blinded to group allocation. The data analysis plan was submitted as part of the trial registration (ISRCTN78666212).

All focus groups and interviews will be audio-recorded, transcribed verbatim, and analysed using qualitative analysis, including content [50–52]- and thematic analysis [53, 54]. The documented data on dose and fidelity will be analysed with descriptive statistics.

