## Methods

### Study design

This study will be carried out as a cluster-randomised parallel trial, with schools as the unit of randomisation and a wait-list control group. The list of schools that will participate will be computer-randomised either to intervention or control with a 1:1 ratio. The randomisation will be performed by a statistician in blocks of two and will be done separately for low and high socioeconomic status schools. The personnel recruiting the schools did not have access to the randomisation sequence. The protocol is reported in accordance with the SPIRIT (Standard Protocol Items: Recommendations for Interventional Trials) 2025 guidelines [30].

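### The baseline comparisons of the arms use student-level tests that ignore the randomised schools, so their p-values are too small (minor: the treatment effect is unaffected)

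*Protocol article*

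**What the plan says.** The Study design section describes a trial "with schools as the unit of randomisation and a wait-list control group". Allocation is "computer-randomised either to intervention or control with a 1:1 ratio", carried out "in blocks of two and will be done separately for low and high socioeconomic status schools".

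The Sample size calculation section allows for clustering. It assumes an "average correlation between cluster of 0.02" and arrives at "27 schools in the intervention group and 27 schools in the control group", each school contributing 50 students.

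The Data analysis section begins with the baseline comparison of the arms. Continuous demographic variables are to be "presented using means and standard deviations (SD) for normally distributed data and compared using independent t-tests". Those that are not normally distributed get medians, ranges and non-parametric tests. Categorical variables are given as proportions, and "group differences will be examined using chi-square tests". None of these tests has a school term. The same paragraph then gives the outcome analyses a mixed model with an individual and a school level. The protocol therefore recognises clustering in its sample size and outcome models, but not in its baseline tests.

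**The concern.** An independent t-test or a chi-square test takes every student as an independent observation. Under school randomisation, students of one school are allocated together and resemble one another, so the difference between arms varies more by chance than the test assumes. The p-values come out too small, and ordinary between-school variation is reported as a significant difference.

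Readers use the baseline table to judge whether randomisation worked and whether the arms are comparable. With several background variables tested, one or more false signals become likely, and the authors would have to explain imbalances that are only what randomising 54 schools produces. The stake is the credibility of that table.

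**Working it through.** **Inputs.** From the Sample size calculation section: ICC = 0.02 (the stated average correlation, read as the intracluster correlation), m = 50 students per school, 27 schools per arm, two-sided 5% level, variance 5. From Study design: blocks of two within low and high socioeconomic strata. The protocol gives no ICC for any demographic variable and no significance level for the baseline tests. Every other ICC below is an assumption, and the 5% level is carried over.

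**The plan's own figure first.** The design effect is DE = 1 + (m − 1) × ICC = 1 + 49 × 0.02 = 1.98. With 0.35 taken as a difference in points, n per arm = 2 × (1.96 + 0.84)² × 5 / 0.35² ≈ 641. Then 641 × 1.98 = 1,269 and 1,269 / 50 = 25.4, which rounds up to 26 schools. One extra school per arm, or a t-based calculation, gives the stated 27. (Read literally as Cohen's d, 0.35 would need only 6 or 7 schools per arm. That is a separate matter.) On the reading that reproduces 27, the sample size already carries a design effect of 1.98.

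**Rejection rate of the unadjusted test.** The true variance of the difference in means is DE times what the t-test assumes. Under sound randomisation a nominal two-sided 5% test therefore rejects with probability 2 × [1 − Φ(1.96 / √DE)].

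| ICC | DE with m = 50 | Actual rejection rate |
|---|---|---|
| 0.005 (assumed) | 1.245 | 7.9% |
| 0.01 (assumed) | 1.49 | 10.8% |
| 0.02 (sample size section) | 1.98 | 16.4% |
| 0.05 (assumed) | 3.45 | 29.1% |
| 0.10 (assumed) | 5.90 | 42.0% |

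At 0.02 the step is 1.96 / √1.98 = 1.393 and 2 × [1 − Φ(1.393)] = 0.164.

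**Simulation.** The set-up was 54 schools of 50, split 27 and 27 between the two strata (assumed), allocated in blocks of two, with 3,000 replicates. The chi-square test was applied to a median-split binary variable, with the ICC on the latent scale. The stratum share is the assumed proportion of between-school variance explained by the socioeconomic strata.

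| ICC | Stratum share | t-test | Chi-square | t-test on school means |
|---|---|---|---|---|
| 0 | none | 5.2% | 5.4% | 5.4% |
| 0.02 | none | 16.1% | 12.1% | 4.9% |
| 0.02 | half | 11.8% | 9.0% | 2.8% |
| 0.10 | none | 42.0% | 33.2% | 4.9% |
| 0.10 | half | 30.6% | 23.1% | 1.0% |

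Three things follow.

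- The formula is confirmed. The test on school means returns to about 5% when the strata explain nothing, so the excess comes from ignoring school.
- Stratification lowers the excess but does not remove it in these scenarios.
- Where the strata matter, a school-level test that leaves them out becomes conservative (2.8% and 1.0%). An adjusted comparison should therefore include the stratum.

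**The case against.** **The covariates are already fixed.** The Data analysis section sets them in advance: the baseline value of the outcome, then gender and parental education, in a model with a school level. This stands. A reader might infer that false baseline differences would steer the choice of covariates or bias the treatment effect. Nothing in the protocol links a baseline p-value to the outcome models.

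**The scope is narrow.** The t-test sentence covers demographic variables. SCAS-S is the primary outcome, and its baseline value enters the model as a covariate. A reader might expect false imbalance in baseline anxiety, but the text does not clearly plan to test it. This stands too.

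**The size is borrowed.** The ICC of 0.02 belongs to the sample size for anxiety. It is tempting to say that socioeconomic and origin variables cluster more strongly by school, and so to lead with the highest rates. The documents give no figure for this, so the range has to be shown from low to high.

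**Stratification helps most where it matters.** Parental education is the trial's socioeconomic indicator and is dichotomised, so the chi-square rates with stratification (9.0% and 23.1% in the scenarios run) are the closer guide for it. This lowers the figures but leaves them above 5%.

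**Baseline comparison can have a purpose.** It would go too far to call it pointless. The article does not make clear whether students join before or after their school is allocated, and it describes parental meetings about the study in intervention schools. If participation differed by arm, a comparison could show it. That defends a comparison which allows for school. An unadjusted test cannot tell selection from ordinary between-school variation.

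**The registered analysis plan is not shown.** It may add detail, and that the tests are at student level is inferred. It is the natural reading, since plain tests on means and proportions are named while the school level is spelled out for the outcome models.

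**Conclusion.** The point holds and is minor. As stated, the baseline tests do not fit a trial that randomises schools, and their p-values are too small. If the ICC of 0.02 applies with 50 students per school, a nominal 5% t-test rejects about 16% of the time. Across assumed ICCs from 0.005 to 0.10 the rate runs from about 8% to 42%, and it is lower for variables that the socioeconomic strata help to balance. These figures assume equal schools of 50, student-level tests and a 5% level.

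The treatment effect estimate is not affected. What suffers is the baseline table, which would tend to signal imbalance where there is only chance variation between schools.

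**What to change.** Remove the t-tests, non-parametric tests and chi-square tests from the baseline paragraph. Describe the arms at both school and student level, with standardised differences, and leave the planned covariates as they are.

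If the team wants to check for differential participation by arm, it should state that purpose and use a comparison that allows for clustering: an analysis of school-level summaries or a mixed model with a school effect, in either case including the socioeconomic stratum.

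The first option costs nothing and shortens the analysis. The second adds a few models of a kind already planned for the outcomes. Neither needs new data or any change to the outcome analyses.

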### The intervention

A logic model of the intervention study, including the intervention components, process evaluation, and outcome evaluation, is described in Table 1.

**Table 1 Tab1:** Logic model of the intervention study

Input	Intervention components	Materials	Implementation strategies	Mediators	Process outcomes	Outcome evaluation
Funding Expert support	Physical activities Homework support with short activity breaks Walking and audiobook	Physical activity inspirational material Digital audio book subscriptions	Workshops with school staff Parental meetings Research support	Competence Autonomy Relatedness	Fidelity Dose Feasibility Acceptability Context	Mental health Cognitive function Academic performance Physical activity Sedentary behaviour Health behaviours BMI

The development of the intervention has been directly informed by barriers and facilitators identified by students and teachers [31]. This information was collected through workshops and interviews during 2021–2022 and used to develop implementation strategies for this study.

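### The outcome models leave out the school-SES stratum used in randomisation, and also wave; clustering is handled, but standard errors may be too wide and precision is given away

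*Protocol article*

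**What the plan says.** The Study design section makes the school the unit of randomisation, with 1:1 allocation "in blocks of two and will be done separately for low and high socioeconomic status schools". The recruitment section spreads enrolment over time: "Three waves are planned: the first in the school year of 2021–2022, the second in 2023–2024, and the third in 2024–2025". It does not say whether the randomisation list was drawn separately for each wave.

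The Data analysis section then sets out the models for all primary and secondary outcomes. They are mixed-effects regressions with students nested in schools. The crude model is described as "including group allocation as a predictor and adjusting for baseline values of the corresponding outcome". The next step is: "In a second model, gender and parental education will be added to the model". Parental education is defined under Background characteristics as a two-level household variable. Neither the school-level SES stratum nor wave is listed in either model.

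**The concern.** When randomisation is balanced on a factor that predicts the outcome, the treatment difference varies less from one randomisation to another than it would without that balance. A model that omits the factor does not see this. Variation between low- and high-SES schools stays in the school variance component, and the reported standard error describes a less precise trial than the one that was run. Confidence intervals come out too wide and the test rejects too seldom under the null.

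Household parental education does not close the gap. It enters only the second model, and it describes the student's home, whereas the stratum describes the school. It can stand in for the stratum only in part.

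The protocol's own Background gives reason to think that these factors could matter. It links low parental education to lower physical activity and academic performance, and it reports that anxiety is rising over time. With recruitment running from 2021 to 2025, school cohorts may differ by calendar period as well as by SES.

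**Working it through.** **Inputs from the Sample size calculation section.** Correlation 0.02, read here as the intraclass correlation (ICC); m = 50 students per school; 27 schools per arm; two-sided alpha 0.05; power 80%; effect 0.35; variance 5.

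**1. The plan's own figure.** The design effect is 1 + 49 × 0.02 = 1.98.
- With 0.35 taken as a standardised effect, as labelled: 129 per arm × 1.98 = 255.4, and 255.4 / 50 = 5.1, so 6 schools per arm (7 with a t correction). This does not give 27.
- With 0.35 taken as raw points against a variance of 5: 0.35/√5 = 0.157 SD; 641 × 1.98 = 1,269 per arm; 1,269 / 50 = 25.4, so 26 schools, or 27 with a t correction (power 81.0%).

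The second reading matches the stated 27 and is used below for the power columns only. The standard-error and alpha results do not depend on it.

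**2. How much of a school mean's variance lies between schools.** In units of the total variance, the variance of a school mean is ICC + (1 − ICC)/m = 0.02 + 0.98/50 = 0.0396. The between-school share is 0.02/0.0396 = 0.505. About half of the variance is therefore at the level where stratum and wave act.

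**3. Effect of leaving out a balanced factor.** Let s be the share of between-school variance that the omitted factor explains. The documents do not give s, so it is an assumption shown as a range.
- True SE / model SE: r = √(1 − 0.505 s)
- Excess of the model SE: 1/r − 1
- Actual alpha: 2[1 − Φ(1.96/r)]
- Model SE of the difference: √(2 × 0.0396/27) = 0.0542; true SE = r × 0.0542
- Power without the factor: 1 − Φ[(1.96 × model SE − 0.157)/true SE]
- Power with the factor: Φ(0.157/true SE − 1.96)

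| s (assumed) | r | model SE too large by | actual alpha | power without | power with |
|---|---|---|---|---|---|
| 0 | 1.000 | 0% | 0.050 | 82.4% | 82.4% |
| 0.10 | 0.974 | 2.6% | 0.044 | 83.0% | 84.3% |
| 0.25 | 0.935 | 7.0% | 0.036 | 84.0% | 87.1% |
| 0.50 | 0.865 | 15.7% | 0.023 | 85.9% | 91.7% |

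**4. Simulation check.** 54 schools were allocated in blocks of two within SES strata, either within wave or ignoring wave, with 8,000 replicates per setting. Four-fifths of s was assigned to the stratum and one-fifth to wave.
- s = 0.25: alpha 0.033–0.034 without the terms and 0.046–0.048 with them; power 82% against 85–86%.
- s = 0.50: alpha 0.023–0.027 without and 0.046–0.050 with; power 84% against 90–91%.
- s = 0: adding the terms changed power by 0 to 1.3 percentage points, all of it a loss.

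**5. Wave.** The table requires that the omitted factor was balanced by the randomisation. The article states this for school SES only. It carries over to wave only if schools were randomised within wave. If they were not, the model standard error without wave correctly reflects the chance imbalance that can occur, and the test is not conservative on that account. What is lost is precision, and any imbalance that does occur across waves stays unadjusted.

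**The case against.** **The clustering is modelled.** A reader might infer that the standard errors ignore the cluster design. They do not: school is the second level of the model. Only the stratification within that design is missing.

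**The error is on the safe side.** Nothing here biases the estimate or inflates the type I error. Nor can it be said that planned power is lost: on the reading that reproduces 27 schools per arm, power without the terms is 82–86% in every row above, and on the literal standardised effect it exceeds 99.9%. Both statements stand.

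**The size is assumed.** No document gives s, and the 0.02 is not described as adjusted for baseline. Both models adjust for the baseline outcome, measured in each wave's own autumn, which should absorb much of any stable SES or cohort difference. This stands too, and it makes the lower rows of the table more plausible for outcomes with a strong baseline.

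**The first wave.** Workshops and interviews in 2021–2022, the school year of the first wave, produced material "used to develop implementation strategies for this study". A reader might infer that the first wave received a weaker programme and that pooling hides this. The article does not say so: it describes one set of components and places staff workshops at the start of each wave. A wave main effect would not reveal dilution in any case.

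**An unseen analysis plan.** The article says that a data analysis plan was submitted with the registration, and its abstract promises adjustment for relevant covariates. Wave checks and sensitivity subsets may properly be left to that plan. The covariate lists are different: the article spells them out for both models, so the missing stratum is a stated choice and not a silence.

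**Conclusion.** The point holds as a recommendation to improve the analysis; it is not a threat to validity. The school-SES stratum should be in both models because the schools were randomised within it. Omitting it makes the standard error about 3% to 16% too large and the actual two-sided alpha about 0.044 to 0.023 if the stratum explains 10% to 50% of the between-school variance. That range is an assumption. The consequence is nil if the stratum is not prognostic, and smaller after baseline adjustment. The corresponding power difference is about 1 to 6 percentage points.

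The case for wave is weaker. It rests on calendar-time differences between cohorts, and the alpha figures apply to it only if randomisation was done within wave. The omission itself is certain from the text; the size of its effect is not.

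**What to change.** Add school-SES stratum (low/high) as a fixed effect in both models for every outcome, and include it in the imputation model. Add wave (three levels) as a fixed effect in both models for precision. State whether schools were randomised within wave. Keep household parental education in the second model as planned, since it does not replace the stratum. These terms should be written into the analysis plan before any unblinded analysis, so that the covariate choice cannot be questioned later.

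The cost is one school-level degree of freedom for the stratum and two for wave, three of the 52 left from 54 schools after intercept and group. If neither factor is prognostic, the simulated power loss is at most about 1 percentage point. No change to design or data collection is needed. A group-by-wave estimate and an analysis restricted to the second and third waves are optional extras; their absence is not an error in the plan.
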